### Statistical analysis

Continuous variables will be expressed as mean ± standard deviation (SD) when normally distributed with homogeneous variance; otherwise, median with interquartile range (IQR) will be reported. Categorical variables will be displayed as numbers and percentages. Baseline characteristics between the two groups will be compared using a two-sample t-test or Pearson’s χ2 test. Linear mixed effects models will be utilized for the analysis of repeated measurement data to estimate the adjusted mean change between the groups from baseline to each follow-up period. Baseline level, time, and treatment will serve as fixed effects, with patients as a random covariate to account for repeated measurements. Results will be reported with 95% confidence intervals (CI). The cumulative probability of MACCE will be compared between groups using Kaplan-Meier curves and log-rank test. Ultrafiltration rate (UFR), along with other clinically relevant factors such as patient characteristics (including age, gender and comorbidities), vascular access and anticoagulation will be indeed included as covariates in the multivariate models for the primary outcome. DKD and the frequency of HDF as preplanned subgroup stratification factors. P-value less than 0.05 denoted statistical significance, and we will use SAS 9.4 (SAS Institute Inc, Cary, North Carolina) and SPSS 23.0 (IBM, USA) for all analyses.

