### Secondary outcomes

The secondary outcomes include:

(1)All-cause mortality at 1year, 2 years and 3 years follow-ups.(2)The incidence of intradialytic hypotension (IDH). According to the National Kidney Foundation Kidney Disease Outcomes Quality Initiative (KDOQI), IDH is defined as “a decrease in systolic blood pressure (SBP) by ≥ 20 mmHg or a decrease in mean arterial pressure (MAP) by ≥10 mmHg, accompanied by hypotension symptoms such as abdominal discomfort, yawning, sighing, nausea, vomiting muscle cramps, restlessness, dizziness or fainting, and anxiety” [17]. In addition, we will compile the proportion of patients with an absolute nadir systolic BP < 90 mmHg (pre-dialysis systolic BP < 160 mmHg) or a nadir BP < 100 mmHg (pre-dialysis BP ≥ 160 mmHg) during HD, as it most potently associated with mortality [18].(3)The incidence of hypoglycemia. A serum glucose level below 3.9 mmol/L (70 mg/dl) is defined as hypoglycemia [19,20]. In addition, three levels of hypoglycemia will be classified according to the American Diabetes Association [21, 22]. Level 1 hypoglycemia: a serum glucose concentration <3.9 mmol/L) but ≥3.0 mmol/L, regardless of hypoglycemia symptoms, including but are not limited to, shakiness, irritability, confusion, tachycardia, sweating, and hunger. Level 2 hypoglycemia: a serum glucose concentration <3.0 mmol/L. Level 3 hypoglycemia: a severe hypoglycemia event (altered mental and/or physical functioning) that requires assistance from another person for recovery, irrespective of glucose level.(4)Blood pressure variability during HD. Systolic blood pressure (SBP) and diastolic blood pressure (DBP) will be measured before HD, every hour during HD, and after HD. Blood pressure coefficient of variation (CVBP) will be used to represent the variability of SBP and DBP during HD. CVBP = standard deviation of blood pressure/ mean blood pressure.(5)Blood glucose variability during HD. Within the first 48 weeks after enrollment, we will measure blood glucose (postprandial blood glucose) during the first HD process each week (0h before HD, 2h during HD and 0h after HD). Blood glucose coefficient of variation (CVBG) = standard deviation of blood glucose/ mean blood glucose.(6)Dysfunction of vascular access.(7)Cardiac function. Left ventricular end diastolic diameter (LVEDD), left ventricular posterior wall thickness (PWTd), interventricular septal thickness (SWTd), and left ventricular ejection fraction (LVEF) will be measured using echocardiography. Meanwhile, we will also calculate relative wall thickness (RWT), left ventricular mass (LVM), and left ventricular mass index (LVMI).(8)Fatigue level: ICFS-10 fatigue rating scale and the 9-item Fatigue Severity Scale (FSS) [23].

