### Sample size determination

Sample size calculation was performed based on the primary outcome MACCE. Our hypothesis posits that the risk of MACCE in the glucose-containing dialysate group will decrease by 25% compared to the glucose-free dialysate group. The Log-rank test was used to compare the primary outcome between groups. We anticipate completing the enrollment within 1 year, and followed by a 3-year follow-up period. We performed sample size calculations with PASS 15.0.5 utilizing an α value of 0.05 and a power of 90%. Accordingly, we require a total of 544 participants (272 per group). Taking into account a potential 10% dropout rate, we determined that 600 participants should be enrolled in this study.

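### The mixed model listed for repeated secondary outcomes has no treatment-by-time term, so it cannot give the between-group change at each follow-up period that the plan sets as its target

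*Protocol article*

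**What the plan says.** Two adjacent sentences in the Statistical analysis section of the protocol article matter here.

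- The target: linear mixed models will be used "to estimate the adjusted mean change between the groups from baseline to each follow-up period".
- The model: "Baseline level, time, and treatment will serve as fixed effects, with patients as a random covariate to account for repeated measurements".

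Results are to carry 95% confidence intervals. The article lists no interaction between treatment and time in this section or any other.

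The Secondary outcomes section shows which outcomes this model could serve. For glucose variability: "Within the first 48 weeks after enrollment, we will measure blood glucose (postprandial blood glucose) during the first HD process each week". For blood pressure variability, systolic and diastolic pressure "will be measured before HD, every hour during HD, and after HD", which yields a coefficient of variation for the dialysis session. Echocardiographic measures and two fatigue scales are also listed, but the visible text does not say how often they are taken. The assessment schedule is in a figure that was not available.

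**The concern.** The two sentences do not fit together. The first asks for a between-group result for each follow-up period. The second lists main effects only, and such a model holds the treatment difference at one constant value throughout follow-up. It can describe an average effect, but not how the effect differs from one period to the next.

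If the effect of glucose-containing dialysate on, say, glucose variability or left ventricular mass builds up or wanes, the model as listed reports too much at some periods and too little at others. Its interval is then centred on the average, not on the period named beside it. Analysts following the text would have to print the same estimate at every visit or depart from the published model once data are in hand.

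**Working it through.** The plan states no figure on this point, so there is none to reproduce. The check is algebra, followed by two illustrations whose inputs are assumed.

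**1. What the listed terms can estimate.** For a patient at follow-up visit k, the listed model is

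Y = b0 + b1 × baseline + time_k + b2 × treatment + patient effect + error.

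Fix the baseline value and subtract the control mean from the treated mean at visit k. The terms b0, b1 × baseline and time_k cancel, leaving b2. Written over the coefficients (intercept, baseline, visit 2, visit 3, treatment), the contrast is [0, 0, 0, 0, 1] at visit 1, at visit 2 and at visit 3. The between-group difference in change from one follow-up visit to another is the zero vector, so the model fixes it at exactly 0. Coding time as a number instead of a category changes nothing, because time still shifts both arms equally.

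Because baseline is held fixed, b2 is also the adjusted difference in change from baseline. There is one such number, not one per period.

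**2. Illustration by arithmetic (assumed trajectory).** Suppose three visits with equal weight and true differences d/3, 2d/3 and d. The single estimate is their mean:

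(d/3 + 2d/3 + d) / 3 = 2d/3.

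| Visit | True difference | Reported | Reported / true |
|---|---|---|---|
| 1 | d/3 | 2d/3 | 2.00 |
| 2 | 2d/3 | 2d/3 | 1.00 |
| 3 | d | 2d/3 | 0.67 |

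A waning effect reverses the pattern, and a constant effect produces no error at all.

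**3. Illustration by simulation (assumed inputs).** 600 patients, the planned enrolment, were split 300 per arm over three visits, with true differences of 0, 0.3 and 0.6, patient SD 0.7, residual SD 0.7, a standard normal baseline with slope 0.5, no missing data, and 60 runs. Only the 600 and the 1:1 split come from the protocol.

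| | Visit 1 | Visit 2 | Visit 3 |
|---|---|---|---|
| Assumed truth | 0 | 0.30 | 0.60 |
| Model as listed, mean estimate | 0.29 | 0.29 | 0.29 |
| Model as listed, 95% CI coverage | 0% | 93% | 0% |
| With treatment × categorical visit, mean estimate | −0.00 | 0.29 | 0.58 |

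The single value is the average of the three interaction estimates: (−0.002 + 0.289 + 0.584) / 3 = 0.29.

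**4. What the interaction costs in precision, under the same assumed SDs.**

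- Averaged difference: variance (2/300) × (0.49 + 0.49/3) = 0.00436, SE 0.066.
- Difference at one visit: variance (2/300) × (0.49 + 0.49) = 0.00653, SE 0.081.
- Ratio: √(0.00653 / 0.00436) = 1.22, so each period-specific interval is about 22% wider than the interval for the average.

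**The case against.** The strongest reply is that this is one sentence in a condensed article. It names factors without saying that there are no interactions, and the full protocol (a supplementary file) or a statistical analysis plan may contain the term. That stands as a limit: a reader might infer that the trial will certainly be analysed without the interaction, and the article alone does not support that. It does not remove the point. The article goes beyond naming a mixed model: it lists the fixed and random effects, and that list does not meet the target set one sentence earlier.

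Second, a main-effects model is not invalid. It estimates a time-averaged effect, which is a legitimate and sometimes preferable summary. This also stands. The fault lies in pairing that model with a period-by-period target, so rewording the target is an acceptable remedy.

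Third, a reader might infer that the trial's year-1 effects would be overstated by 100% and its year-3 effects understated by 33%. The documents do not support this. The visible text gives 1, 2 and 3 years for all-cause mortality only, gives no annual schedule for echocardiography or fatigue, and says nothing about effects growing in equal steps. Those percentages follow from an assumed trajectory and show the mechanism, not the harm in this trial.

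Fourth, a reader might suppose that the main result is at risk. It is not. MACCE is compared by Kaplan-Meier curves and the log-rank test, and the sample size rests on that comparison.

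Finally, a full visit-by-visit model would be costly for weekly glucose. With 48 weekly levels, treatment × week and baseline × week add 47 + 47 = 94 parameters, and an unstructured covariance has 48 × 49 / 2 = 1,176. This stands, and it shapes the fix.

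**Conclusion.** The point holds as a contradiction between the stated target and the listed model. With fixed effects of baseline, time and treatment, the model returns one averaged difference, correct at every follow-up period only if the effect is constant from the first period on. The article does not assume that.

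The scope is limited to continuous secondary outcomes measured repeatedly: blood pressure and glucose variability and, where repeated, echocardiography and fatigue. The primary analysis is untouched. The algebra rests on no assumption beyond the terms listed. The size of the distortion cannot be stated for this trial because it depends on the unknown course of the effect and on how much data each visit contributes. An unseen analysis plan may already include the interaction, in which case only the published text needs correcting.

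**What to change.** For each repeated continuous secondary outcome, choose one of two routes and say which.

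- **Period-specific effects wanted:** add a treatment-by-time interaction, with time as a categorical follow-up period, and report the between-group contrast at each period with its 95% confidence interval. Group the weekly glucose measurements into a few periods. For example, four periods of 12 weeks (4 × 12 = 48) would need 3 interaction parameters in place of 47.
- **One overall effect wanted**, for instance for weekly glucose variability: keep the listed terms and restate the target as the average between-group difference over follow-up.

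Baseline-by-visit terms, an unstructured covariance and a named main visit are optional, since the contradiction is cured without them.

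The cost is a sentence or two of text, one extra parameter for each period after the first, and wider period-specific intervals (about 22% wider under the assumed SDs in the working). The article describes the trial as still recruiting, with results due after three years of follow-up, so the change can be made before analysis.

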### Participants

All patients requiring maintenance HD will be assessed for eligibility. Both diabetic and non-diabetic patients will be included in the study. Details regarding diabetes pharmacotherapy, including oral hypoglycemic agents and insulin regimens, will be systematically documented. The inclusion criteria are as follows: (1) Age between 18 and 75 years; (2) Having undergoing maintenance HD three times a week for at least three months and the dialysis modality has remained stable; (3) Kt/v ≥ 1.2 in the last 8 weeks before entering the study; (4) Provision of informed consent prior to any study specific procedures. And the exclusion criteria include: (1) Participants with life expectancy less than 1 year; (2) Participants hospitalized due to decompensation or any other complications of diabetes within 3 months; (3) Participants under active infection or active cancer treatment; (4) Receiving glucose-containing dialysates in the past 3 months or intolerance to glucose-containing dialysates; (5) Planned coronary intervention, or cardiac treatment (e.g., valve); (6) Participation in another clinical intervention trial within the last 3 months; (7) Pregnancy, or impending miscarriage; and (8) Inability of the patient to understand or comply with the study.

Eligible patients will be informed clearly of the objective, procedure, expected benefits, and possible risks involved. Both the patient and treating physicians are required to complete and sign the informed consent form. Confidentiality of all patient information will be maintained, and patients have the right to withdraw from the study at any time without facing any prejudice.

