### Randomization and blinding

After obtaining the written informed consent (S4 File), eligible patients will be randomized in a 1:1 ratio to receive either glucose-containing or glucose-free hemodialysis dialysate, with allocation determined by a centrally computer-generated randomization sequence. To ensure balance between groups, we will implement stratified block randomization using diabetic kidney disease (DKD) status as the stratification factor. Participants will be categorized into DKD and non-DKD subgroups, with each stratum undergoing separate randomization using computer-generated sequences with randomly permuted block sizes of 4 or 6 to maintain the 1:1 allocation ratio while preventing predictability in treatment assignment. Group A will receive glucose-containing dialysate for HD, and group B will receive glucose-free dialysate. Due to practical considerations, blinding of patients and treating clinicians was clinically impractical during this study. But the outcome assessors and data analysts will be fully blinded throughout the study to minimize bias.

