## 3. Discussion

This trial is a prospective, open-label, multicenter RCT aimed at evaluating both the efficacy and safety of 5.5 mmol/L glucose-containing dialysate for maintenance HD patients. Asymptomatic hypoglycemia occurs in approximately 40% HD patients using glucose-free dialysate [24]. Blood glucose can be dialyzed out through the dialysis membrane as it is a small molecule. Additionally, a considerable number of ESKD patients experience obvious gastrointestinal symptoms that may reduce their food intake, leading to malnutrition and a tendency towards hypoglycemia before dialysis. Blood glucose loss during HD, malnutrition and tight glycemic control all contribute to the occurrence of hypoglycemia in HD patients [25–27]. Hypoglycemia can result in fundus hemorrhage, angina, anemia, and even coma and death, which indeed increase mortality of ESKD patients [3]. Therefore, preventing the occurrence of hypoglycemia in dialysis patients is an urgent issue.

Several studies had reported the benefits of glucose-containing dialysate in reducing incidence of hypoglycemia and improving heart rate variability in maintenance HD patients [8–10,28]. However, these studies were all observational with small sample sizes, and there is still no definitive evidence on the long-term prognosis of maintenance HD patients using glucose-containing dialysate. Furthermore, there are ongoing controversies regarding the benefits of glucose-containing dialysate, as several studies have not identified it as a superior choice for all maintenance HD patients [6,14]. Glucose-containing dialysate may stimulate oxidative stress, induce hypertriglyceridemia and less effective in potassium removal during HD [6].

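### The model for blood glucose variability omits baseline diabetes drug class, a recorded predictor; the comparison stays unbiased but is less precise than it could be

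*Protocol article*

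**What the plan says.** All references are to the protocol article.

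- **Participants.** "Both diabetic and non-diabetic patients will be included in the study". On drugs: "Details regarding diabetes pharmacotherapy, including oral hypoglycemic agents and insulin regimens, will be systematically documented". The sentence stands with the eligibility criteria, so a record at baseline is the natural reading. It does not say whether recording continues during follow-up.
- **Discussion.** "Blood glucose loss during HD, malnutrition and tight glycemic control all contribute to the occurrence of hypoglycemia in HD patients".
- **Secondary outcomes.** Incidence of hypoglycemia and CVBG are both listed. Glucose is measured at one session a week over 48 weeks, at three time points per session.
- **Statistical analysis.** For repeated measurements: "Baseline level, time, and treatment will serve as fixed effects, with patients as a random covariate to account for repeated measurements". Further covariates (ultrafiltration rate, patient characteristics including comorbidities, vascular access, anticoagulation) "will be indeed included as covariates in the multivariate models for the primary outcome". Subgroups: "DKD and the frequency of HDF as preplanned subgroup stratification factors".
- **Randomization and blinding.** "we will implement stratified block randomization using diabetic kidney disease (DKD) status as the stratification factor", and "blinding of patients and treating clinicians was clinically impractical during this study".

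No section uses the drug data in an analysis of a glycemic outcome, and the article states no model for the incidence of hypoglycemia.

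**The concern.** The article treats diabetes drugs as worth recording for every patient and treats tight control as a contributor to hypoglycemia. It then writes down a model for the glycemic repeated measures that has no drug term, and it attaches prognostic covariates to MACCE only. This is more than silence that an analysis plan would fill, because the fixed effects are listed.

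In a population that mixes diabetic and non-diabetic patients, drug class is likely to account for part of the between-patient spread in CVBG. Diabetic kidney disease (DKD) status is a stratification and subgroup factor but is not listed in the mixed model, so the model does not pick up that spread by another route, except through baseline level. A prognostic baseline variable left out of the model stays in the residual variance and widens the confidence interval. At stake is the precision of a secondary comparison close to the trial's rationale.

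**Working it through.** No figure in the article is in dispute, and it gives no standard deviation, R-squared or drug-use rate. Everything numerical below is therefore an assumption shown over a range.

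**1. Precision.** Let R² be the share of the variance remaining after baseline level that baseline drug class explains. The standard error with the covariate, relative to that without, is √(1 − R²). The equivalent gain in sample size is 1/(1 − R²).

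| Assumed R² | √(1 − R²) | Fall in SE | 1/(1 − R²) |
|---|---|---|---|
| 0.02 | 0.990 | 1% | 1.02 |
| 0.05 | 0.975 | 2.5% | 1.05 |
| 0.10 | 0.949 | 5% | 1.11 |
| 0.20 | 0.894 | 11% | 1.25 |

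**2. What decides where in the range the gain falls.** Take an illustrative mix of 25% on insulin, 15% on oral agents only and 60% on neither, with mean CVBG of 0.26, 0.22 and 0.16.

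- Overall mean: 0.25 × 0.26 + 0.15 × 0.22 + 0.60 × 0.16 = 0.194.
- Between-class variance: 0.25 × 0.066² + 0.15 × 0.026² + 0.60 × 0.034² = 0.00188.
- Part due to insulin versus oral agents among the treated 40%: 0.40 × 0.625 × 0.375 × 0.04² = 0.00015, or 8% of 0.00188.
- The other 92% is treated versus untreated, which largely follows diabetic status.

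With nothing else in the model and a within-class SD of 0.08, drug class explains 0.00188/(0.00188 + 0.0064) = 23% of the variance. If DKD were already in the model, and all drug users were in the DKD stratum, it would add only 0.00015/(0.00015 + 0.0064) = 2.3%, and the standard error would fall by 1 − √0.977 = 1.1%. A baseline CVBG in the model would absorb part of the same variance.

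**3. Bias.** A simulation used 600 patients, 1,500 replicates, one outcome per patient and randomization stratified by diabetes, with 40% diabetic and 70% of those on drugs (all assumed).

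- With no drug changes that differ by arm and no true effect, the model with baseline level only gave a mean estimate of −0.0004 and a type I error of 4.8%.
- Adding diabetes and baseline drugs moved the standard error from 0.0922 to 0.0909, a fall of 1.4%.

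**4. Drug changes after randomization.** The same simulation was run with a direct effect of 0.30 and drug increases more likely in the glucose arm.

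| Model | Estimate |
|---|---|
| Baseline level only | 0.240 |
| Plus diabetes and baseline drugs | 0.241 |
| Plus drug change after randomization | 0.254 |

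The first two estimate the total effect, drug changes included, so a baseline covariate does not alter what is estimated. The third recovers neither the total effect nor the direct effect of 0.30, because it conditions on a consequence of treatment.

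**The case against.** The strongest case against is that this is an efficiency preference on a secondary outcome. A mixed model with baseline level, time and treatment is standard and valid under randomization. Covariates for secondary outcomes are commonly left to the analysis plan, and neither that plan nor the full protocol (S3 File) is shown. Most of what drug class would explain is diabetic versus non-diabetic, which stratification by DKD largely balances, so the gain beyond DKD may be only 1% to 2%. Chance imbalance is also minor. With 120 DKD patients per arm (40% of 300) and half of them on insulin, the 95% range is 1.96 × √(2 × 0.25/120) = 12.7 points. Even that extreme moves mean CVBG by 0.127 × 0.04 × 0.4 = 0.002, against a standard error of 0.091 × √(2/300) = 0.0074.

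Much of this stands. The model is valid, chance imbalance is already within the confidence interval, and the gain may be small. Two parts do not settle the matter. The article lists its fixed effects, so the point concerns what is written; if the analysis plan has more terms, the article should agree with it. And the 1% to 2% figure presumes that DKD is in the analysis model. The article balances on DKD and plans subgroups by it, but does not list it in the mixed model, so drug class would also recover the diabetic versus non-diabetic variance.

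Whether baseline level already stands in for drug therapy cannot be decided here. The text places glucose sampling after enrollment, but the assessment schedule is in a figure that is not shown, and estimating change from baseline presupposes some baseline value.

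**Conclusion.** The point holds as a loss of precision in the stated model for CVBG. On an assumed extra R² of 0.02 to 0.20, the standard error would be about 1% to 11% smaller with baseline drug class in the model, and nearer 1% if a baseline CVBG is available and DKD is also adjusted for. The MACCE analysis is untouched.

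Three stronger readings are tempting, and the article does not support them.

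- **Confounding by drugs at baseline.** Randomization protects against this, and the simulation shows no bias.
- **A dialysate effect hopelessly mixed with drug changes by unblinded clinicians.** The article reports no such changes. If they occur, they are part of the intention-to-treat effect, and baseline adjustment would neither remove them nor be meant to.
- **A defective hypoglycemia model.** The article states none, so there is nothing to call wrong; the covariate can only be recommended for whichever model is chosen.

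**What to change.** In the Statistical analysis section, add baseline diabetes drug class (none, oral agents only, insulin), fixed at its pre-randomization value, as a fixed effect in the mixed model for CVBG. Use the same covariate in whatever model is specified for hypoglycemia. State that drug use after randomization is not adjusted for and that the intention-to-treat estimate includes any drug changes during the trial.

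If drugs are recorded during follow-up, a descriptive table of therapy by arm may help readers interpret the glycemic results. It would not isolate the effect of the dialysate.

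The cost is a sentence or two, using a baseline value that the Participants section already has recorded, with no added patients or procedures. The optional table depends on follow-up recording, which the article does not confirm.

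### Randomisation is stratified by DKD, but the primary log-rank test as written has no stratum; stratifying it is a free, modest gain in efficiency

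*Protocol article*

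**What the plan says.** Under Randomization and blinding, the protocol article states that "we will implement stratified block randomization using diabetic kidney disease (DKD) status as the stratification factor". Each of the two strata has its own sequence, with "randomly permuted block sizes of 4 or 6 to maintain the 1:1 allocation ratio". No other stratification factor is named.

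Under Sample size determination: "The Log-rank test was used to compare the primary outcome between groups". Under Statistical analysis: "The cumulative probability of MACCE will be compared between groups using Kaplan-Meier curves and log-rank test". Neither sentence mentions a stratum.

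The Statistical analysis section then lists ultrafiltration rate and other factors, with age, gender, comorbidities, vascular access and anticoagulation as examples, which "will be indeed included as covariates in the multivariate models for the primary outcome". DKD is not in that list by name. The fixed effects of the linear mixed models are the baseline value, time and treatment; DKD is not among them either. The one role that DKD is given by name is this: "DKD and the frequency of HDF as preplanned subgroup stratification factors".

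**The concern.** Blocking within DKD strata makes the two arms nearly equal in their DKD mix. If DKD predicts MACCE, chance imbalance in DKD is a source of variation that the design has already removed. An unstratified log-rank test still allows for it in its variance. The test statistic is then less variable under the null than the standard normal it is referred to, so the true type I error falls below 5% and power falls with it. A test stratified by DKD compares patients only within the groups in which they were randomised, and it recovers that loss.

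What is at stake is efficiency and agreement between design and analysis. There is no risk of excess false positives.

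**Working it through.** **The plan's own figure.** The article gives 544 patients (272 per arm), α 0.05, 90% power and a 25% reduction in risk, but no control event rate and no sidedness. The 544 can therefore be neither confirmed nor refuted.

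- Read as a hazard ratio of 0.75, two-sided, the Schoenfeld formula gives 4 × (1.960 + 1.282)² / (ln 0.75)² = 508 events. That is 508/544 = 93% of patients.
- Read as a risk ratio of 0.75, a figure near 544 arises two-sided when the control risk is about 54–55%. At 55% the treated risk is 0.75 × 0.55 = 0.4125, and the implied hazard ratio is ln(1 − 0.4125)/ln(1 − 0.55) = 0.666. N is then 530 (Schoenfeld) or 545 (Freedman).

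**Inputs for the check.** From the article: N = 544, 1:1 allocation within DKD strata, permuted blocks of 4 or 6, 1-year accrual, 3-year follow-up, α 0.05 (taken as two-sided). Assumed, because the article does not give them: 40% DKD, exponential event times, a DKD hazard ratio for MACCE between 1 and 3, and these settings:

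- Set A: control 3-year risk 55%, treatment hazard ratio 0.666; follow-up 3 to 4 years; 5,000 runs.
- Set B: control 3-year risk 30%, treatment hazard ratio 0.58 (power near 90% at that event rate); follow-up 3 to 4 years; 5,000–6,000 runs.
- Set C: hazard centred (on the log scale) at 0.22 per year, treatment hazard ratio 0.67, 3 years, balanced allocation within strata; 4,000 runs.

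**Method.** For each simulated trial, U = Σ(observed − expected events in one arm) and V = Σ(hypergeometric variance). The unstratified statistic is Z = U/√V over all patients. The stratified statistic is Z = (U₁ + U₂)/√(V₁ + V₂) over the two DKD strata. Reject if |Z| > 1.96.

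**Results (unstratified vs stratified).**

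| Set | DKD hazard ratio | Type I error, % | Power, % | Power lost, points |
|---|---|---|---|---|
| A | 1 | 5.2 vs 5.2 | 93.5 vs 93.6 | 0.1 |
| A | 1.5 | 4.8 vs 5.2 | 92.7 vs 93.0 | 0.3 |
| A | 2 | 4.1 vs 5.3 | 92.2 vs 93.2 | 1.0 |
| A | 3 | 3.2 vs 5.0 | 89.9 vs 93.5 | 3.6 |
| B | 1 | 4.9 vs 4.9 | 91.0 vs 90.9 | −0.1 |
| B | 1.5 | 4.9 vs 4.9 | 91.1 vs 91.2 | 0.1 |
| B | 2 | 4.5 vs 4.9 | 90.5 vs 91.3 | 0.8 |
| B | 3 | 4.0 vs 5.1 | 89.4 vs 91.3 | 1.9 |
| C | 1.5 | 4.8 vs 4.9 | 85.4 vs 85.9 | 0.5 |
| C | 2 | 4.3 vs 4.6 | 85.5 vs 87.1 | 1.6 |
| C | 2.5 | 3.8 vs 4.8 | 84.1 vs 86.5 | 2.4 |

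Monte Carlo standard error in sets A and B is about √(0.05 × 0.95/5000) = 0.3 points for type I error and √(0.9 × 0.1/5000) = 0.4 points for power. In set C it is about 0.3 and 0.5 points. Values slightly above 5% are within that error.

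**Cross-check of the mechanism.** In set A under the null, the variance of the unstratified Z was 0.926 at a DKD hazard ratio of 2 and 0.831 at 3; the stratified Z had 1.006 and 1.000. Treating Z as normal, the rejection rate is 2 × [1 − Φ(1.96/√0.926)] = 4.2% and 2 × [1 − Φ(1.96/√0.831)] = 3.2%. These match the simulated 4.1% and 3.2%. The conservatism is the shrunken variance of Z.

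**The case against.** The strongest objection is that the article never calls the test unstratified. It is a condensed account; the full protocol is a supplementary file, an SAP may exist, and either could specify a stratified test. That stands as a caveat. It does not remove the point, because the article is not merely silent about DKD: it names the test twice, gives covariates for the adjusted models and the fixed effects of the mixed models, and places DKD in the subgroup analysis. Followed as written, that is a plain log-rank test.

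Second, the covariate list is open-ended and includes comorbidities, so diabetic disease may enter the adjusted models. That also stands: the article leaves DKD's role there unclear and does not exclude it. But those models are separate from the log-rank test, and a general comorbidity term is not the stratum as randomised.

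Third, the loss depends on DKD being prognostic for MACCE, which the article does not quantify. This is correct, and it is why the range starts at nil. Choosing DKD as the only stratification factor suggests that the investigators expect it to matter, but that is an inference.

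A reader might also infer that the test is invalid, or that power is being lost in a trial already short of events. The first is wrong: type I error stays at or below nominal within simulation error. The second cannot be shown, because without a control event rate the expected number of events is unknown. A reader might add that the unstratified hazard ratio is pulled towards 1. The direction is plausible when a prognostic factor is omitted, but the attenuation was not estimated here and no size is claimed for it.

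**Conclusion.** The point holds as a modest mismatch between design and analysis. The stratum used to randomise is not carried into the primary test as the article describes it. The cost depends on how strongly DKD predicts MACCE: essentially none at a hazard ratio of 1 to 1.5, about 1 to 1.6 points of power at 2, and about 2 to 3.6 points at 2.5 to 3. True type I error is about 4.1–4.5% at a hazard ratio of 2 and 3.2–4.0% at 3, so the error is on the safe side.

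These figures rest on an assumed 40% DKD share, exponential event times, and assumed event rates and treatment hazard ratios, none of which the article states. The missing control event rate and the undefined scale of the 25% reduction matter far more for power. At a hazard ratio of 0.75, two-sided, 544 patients give about 41% power at a 30% control risk and about 66% at 55% (Schoenfeld). That is a separate matter and adds nothing to the size of this one.

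**What to change.** State that the primary comparison of MACCE is a log-rank test stratified by DKD status as recorded at randomisation. Report the hazard ratio with its 95% CI from a Cox model stratified by the same factor. Include the DKD stratum as a fixed effect in the linear mixed models. The subgroup analysis by DKD can stay as planned, and overall Kaplan-Meier curves can still be shown.

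If the SAP or full protocol already specifies this, bring the Sample size determination and Statistical analysis sections into line with it.

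The cost is about one sentence for the primary analysis and one term in the mixed models. With two large strata (about 218 and 326 of 544 patients at a 40% DKD share), stratifying shows no visible penalty even when DKD has no effect: in set A at a DKD hazard ratio of 1, power is 93.6% stratified and 93.5% unstratified. The article reports the trial as still recruiting, with 3 years of follow-up to come, so the change can be fixed well before any comparison of the arms.
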